### Strategies to improve adherence to interventions {11c}

We will fix a researcher to perform the pre-surgical assessment and sign the informed consent form. The researcher will conduct a pre-anaesthetic assessment the day before the procedure, with strict exclusion and inclusion criteria. During the process of obtaining informed consent from the participants, the researcher will explain in detail what the study is about and the need for cooperation. In addition, another researcher who is unaware of the grouping will administer a brief 3–5-min questionnaire to participants within 48 h of the procedure without unduly interrupting their rest time.

### Relevant concomitant care permitted or prohibited during the trial {11d}

All study participants will receive standard post-operative care in the operating room, post-anaesthesia care unit (PACU) and wards.

### Provisions for post-trial care {30}

At the end of the trial intervention, participants will be removed from the LA injection catheter in the safe and comfortable environment of the ward and will be closely observed. Be alert to any risks associated with the study. The follow-up 8 h after the end of infusion will focus on LA-toxicity assessment. In the event of any adverse events, appropriate care and treatment will be provided by our study team and the hospital.

### Outcomes {12}

#### Primary outcome

The primary outcome is the cumulative PCA consumption, including the sum of background dose and self-control dose.

#### Secondary outcomes

The static and dynamic pain scores at 2, 6, 12, 24 and 48 h postoperatively. Pain is scored using a visual analogue scale (VAS), with a score of 0–10 representing pain levels ranging from no pain at all to intolerably severe pain. Dynamic pain is the pain felt when the arm is externally rotated 45° on the side of the operation.The occurrence of PMPS. Defined as chronic pain not related to incision healing, which may be burning pain, pins and needles, tenderness-induced pain, or deep dull pain at the surgical or surgery-related site, and which occurs for at least 4 days in a week after surgery [10, 11].The levels of inflammation-related cytokines. Concentrations of CRP, IL-6, IL-10 and TNF-α in venous blood 1 day before, 2, 6, 12, 24 and 48 h after surgery.Concentration of ropivacaine in venous blood 1, 2 and 3 days after surgery.Total consumption of additional analgesics. Remedial analgesia using parecoxib sodium dosage and the use of additional analgesics during the entire 12-month follow-up period.Post-operative adverse reactions. Including but not limited to PONV, drowsiness, itching, respiratory depression and urinary retention.Post-puncture adverse reactions. Including but not limited to haematoma, infection, nerve damage and abnormal sensation in the blocked area.Postoperative recovery, including the length of stay in PACU, time of first ambulation, intake of food, voiding, gastrointestinal function, length of stay in hospital and the quality of Recovery-15 (QoR-15) questionnaire at 24 h and 48 h after surgery and on the day of discharge [9]. Discharge criteria: vital signs are normal; wound healing is good, with no obvious postoperative complications, such as wound infection, flap necrosis, or fluid accumulation due to poor drainage; pain is mild and does not require medication or oral analgesic medication to achieve satisfactory analgesia; gastrointestinal function is normal; able to get out of bed and move around freely; intravenous fluids are not required; and the patient is willing and wants to be discharged from the hospital.

### Participant timeline {13}

**Fig. 1 Fig1:**
[figure not shown]
The participant timeline is shown in Fig. 1 Time schedule of enrolment, interventions, assessments and visits for participants. PACU, post-anaesthesia care unit; ESPB, erector spinae plane block; VAS, visual analogue scale; PMPS, post-mastectomy pain syndrome; QoR-15, Quality of Recovery-15 questionnaire

### Sample size {14}

The focus of this trial is to look at post-operative pain in the presence of a continuous infusion of LA. Therefore, the expected sample size is calculated based on post-surgical pain scores. Considering that ethnic and geographical differences may have some influence on the perception of pain, we chose the results of a study at another hospital that is geographically close to the location of the current study unit as the basis for the sample size calculation. Based on the results of this study and our pre-experiment, the dynamic VAS at 48 h after MRM surgery is 4.2 ± 1.4 (mean ± standard deviation) for the control group and 3.6 ± 1.1 for the ESPB group [12]. We chose *α* = 0.05, test validity *β* = 80%, and calculated 71 cases per group using PASS 15.0 software. This study is a single-centre study and there may be a degree of bias if the sample size is small, so the shedding rate needed to be increased and is set at 11%. The final sample size is extrapolated to 80 cases per group, including a total of 160 participants.

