**Methods:**

In this prospective, randomised, controlled trial, we will recruit 160 patients, aged 18–80 years, scheduled for elective MRM surgery under general anaesthesia. They will be randomly assigned to two groups: a continuous ESPB group (group E) and a sham block group (group C). Both groups of patients will have a nerve block (group C pretended to puncture) and an indwelling catheter fixed prior to surgery. Electronic pumps containing LA are shielded. The primary outcome is the total consumption of analgesic agents. The secondary outcomes include the levels of inflammation-related cytokines; the occurrence of chronic pain (post-mastectomy pain syndrome, PMPS); static and dynamic pain scores at 2, 6, 12, 24 and 48 h postoperatively; and post-operative and post-puncture adverse reactions.

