Although ESPB was used with definite effectiveness for post-surgical analgesia, most clinical applications were currently for a single injection of LA [7–9]. Theoretically, the maximum duration of a single dose of LA is 12 h [21]. In contrast, continuous administration of the LA after placement of the catheter can provide a longer duration of analgesia. A multicentre, high-quality RCT showed that nerve block with a single injection of LA improved acute pain after breast cancer surgery but did not reduce the incidence of chronic pain [22]. There are still few studies on the use of continuous ESPB in analgesia for MRM surgery, and our research on this occasion is much needed.

Poorly controlled acute pain after surgery is an important contributor to chronic pain and stress and inflammatory responses [23]. We believe that improving acute pain within 48 h of surgery is even more important and therefore used it as the primary outcome for this study. We also evaluated the postoperative recovery in a multidimensional manner by comparing the incidence of PMPS, the QoR-15 score, the concentration of perioperative inflammatory cytokines, total consumption of analgesic agents and post-surgical adverse effects.

In summary, our single-centre, prospective, double-blind RCT will reveal the effect of continuous ESPB on postoperative pain and inflammatory response in patients undergoing MRM surgery and is expected to provide a strong scientific basis for its use in the management of MRM surgery postoperatively. Continuous ESPB and up to 12 months of follow-up are two innovations of this trial. In addition, our results may be extrapolated to other chest procedures and comparisons with the application of different concentrations of local anaesthetics.

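### The sample size and its 80% power belong to dynamic VAS at 48 h, listed as secondary; none is stated for PCA consumption, and the article names the primary outcome inconsistently

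*Protocol article*

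**What the plan says.** The protocol article describes the primary outcome in three ways and sizes the trial on a fourth quantity.

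- **Primary outcome** (under Outcomes {12}): "The primary outcome is the cumulative PCA consumption, including the sum of background dose and self-control dose".
- **Abstract, Methods**: "The primary outcome is the total consumption of analgesic agents". This is wider than PCA alone.
- **Discussion**: "We believe that improving acute pain within 48 h of surgery is even more important and therefore used it as the primary outcome for this" (final word omitted here). The sentence after it places total analgesic consumption among the further evaluations.
- **Secondary outcomes**: "The static and dynamic pain scores at 2, 6, 12, 24 and 48 h postoperatively". Two kinds of score at five times make ten VAS comparisons, and dynamic VAS at 48 h is one of them.
- **Sample size {14}**: "Therefore, the expected sample size is calculated based on post-surgical pain scores". Its control-group input is "the dynamic VAS at 48 h after MRM surgery is 4.2 ± 1.4 (mean ± standard deviation) for the control group". Against this it sets, for the block arm, "3.6 ± 1.1 for the ESPB group", with α = 0.05 and 80% power (printed as β). From these the authors "calculated 71 cases per group using PASS 15.0 software" and, with 11% dropout, set 80 per group and 160 in total.

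No section gives an expected mean, SD or target difference for PCA consumption.

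**The concern.** A trial's sample size should support the test on which its main conclusion rests. Here the calculation supports one of ten VAS comparisons in the secondary list, while the declared primary test is on PCA consumption. Two things are at stake.

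First, if the PCA comparison is not significant, there is no planned difference to judge it against. A reader could not tell whether a worthwhile effect had been excluded or the trial was too small to see it.

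Second, Sample size {14} and the Discussion lean towards pain as the main outcome, while the abstract and the Primary outcome section lean towards consumption. Unless this is settled before unblinding, either could later be presented as primary with some support in the text.

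**Working it through.** **Inputs.** Means 4.2 and 3.6, SDs 1.4 and 1.1, 80% power and 11% dropout come from Sample size {14}. Two-sided 0.05 comes from Statistical methods {20a}, and 1:1 allocation from Sequence generation {16a}.

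**Step 1: reproduce the plan's figure.**

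- Difference: 4.2 − 3.6 = 0.6.
- Root-mean-square SD: √((1.4² + 1.1²)/2) = √1.585 = 1.259.
- Standardised difference: 0.6/1.259 = 0.477.
- Normal approximation: n = 2 × 1.585 × (1.960 + 0.842)²/0.6² = 69.1, so 70 per group.
- Noncentral t: noncentrality = 0.6/√(3.17/n). At n = 70 power is just under 80% (79.95%). At n = 71 it is 80.5%. The smallest adequate n is therefore **71**, with equal or unequal variances.
- Dropout: 71/(1 − 0.11) = 79.8, so **80** per group. With all 80 evaluable, power for this VAS comparison is 85.0%.

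The stated 71 and 80 are correct for dynamic VAS at 48 h.

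**Step 2: what these numbers imply for PCA consumption.** With no PCA mean, SD or target difference in the document, no single power figure can be computed. Over an assumed range of standardised differences d (two-sided t-test at 0.05):

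| Assumed d in PCA consumption | Power, 71 per group | Power, 80 per group |
|---|---|---|
| 0.2 | 22.0% | 24.2% |
| 0.3 | 42.7% | 47.1% |
| 0.4 | 65.8% | 71.0% |
| 0.5 | 84.1% | 88.2% |
| 0.6 | 94.4% | 96.5% |
| 0.8 | 99.7% | 99.9% |

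**Step 3: detectable difference at 80% power.**

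- Normal approximation: d = (1.960 + 0.842) × √(2/n) = 0.470 at 71 per group and 0.443 at 80.
- Noncentral t: 0.473 at 71 per group and 0.446 at 80.
- Statistical methods {20a} moves to Mann–Whitney if the data are non-normal. Under normality that test needs a difference larger by √(π/3) = 1.023, so 0.473 × 1.023 = 0.484 SD at 71 per group. For skewed or heavy-tailed data the figure could be higher or lower.

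**Step 4: why the VAS assumption does not carry over.** The Description for Intervention sets the PCIA at 100 µg sufentanil in 100 ml (1 µg/ml), with a 1.5 ml/h background and 1.5 ml self-controlled doses. Over an assumed full 48 h, an unchanged background delivers 1.5 × 48 = 72 ml, or 72 µg, in both groups. Any group difference in the total must then come from the self-controlled doses alone. A 0.6-point VAS difference says nothing definite about the size or spread of that component.

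**The case against.** The strongest defence is that pain really is the intended primary outcome. Sample size {14} gives postoperative pain as the trial's focus, and the Discussion calls acute pain within 48 h primary, so the calculation may sit where the authors meant it to. This has force: it would be wrong simply to declare VAS secondary and leave the Discussion contradicting that. It does not rescue the plan. The Primary outcome section and the abstract say otherwise, and acute pain within 48 h does not single out dynamic VAS at 48 h from the ten listed scores.

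A second defence is transparency: Sample size {14} names the variable it uses, so a careful reader is not misled. That is true, and it makes the repair easy. It does not supply the missing basis for the PCA comparison. Nor is this a gap left by condensing a full protocol into an article, because the calculation is printed in full and its choice of variable is argued for.

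A reader might infer that the trial is underpowered, or that 71 per group is a miscalculation. The documents support neither. The VAS figure is right, and 71 per group is enough for PCA consumption if the true difference is about 0.47 SD or more. A detectable difference in micrograms cannot be given either. The article offers no PCA SD, and it mentions its pre-experiment only in connection with the block and the VAS values, never as a source of PCA data.

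**Conclusion.** The point holds as an inconsistency between outcome and sample size. The 80% power belongs to dynamic VAS at 48 h. For the outcome named in the Primary outcome section, power is unstated: with 71 per group it runs from 22% to over 99% across assumed differences of 0.2 to 0.8 SD, and reaches 80% at about 0.47 SD (0.45 SD at 80 per group). These figures assume a two-sided t-test at 0.05; Mann–Whitney under normality needs about 0.48 SD at 71 per group. The disagreement among the abstract, the Primary outcome section and the Discussion makes correction necessary, because the right repair depends on which outcome is primary. Whether power for PCA consumption is adequate remains open.

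**What to change.** Keep 160 patients and proceed in this order.

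1. By a documented, dated amendment before unblinding, make the abstract, Primary outcome, Secondary outcomes, Sample size {14} and Discussion name one and the same primary outcome.
2. **If PCA consumption stays primary**, state in Sample size {14} that the 80% power is for dynamic VAS at 48 h, a secondary outcome. Then add that 71 evaluable per group gives 80% power at two-sided 0.05 for about 0.47 SD in PCA consumption by t-test (about 0.48 SD by Mann–Whitney under normality; 0.45 SD by t-test at 80 per group). Convert this to PCA units with an SD whose source is given, and set it against a stated target difference. Note that an unchanged background infusion is common to both groups, so the difference must arise in the self-controlled doses.
3. **If pain is the intended primary outcome**, name dynamic VAS at 48 h explicitly, so that the existing calculation applies as it stands, and move PCA consumption to the secondary list.

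The cost is rewording plus the ethics committee approval that the section on protocol amendments {25} requires. No patients are added. The stated power for the primary outcome may look less favourable than the present text suggests. Dissemination plans {31a} puts deblinding at the end of the study, so at the stage the article describes there was still time to do this.

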### Recruitment {15}

Our hospital provides healthcare to over 4 million people in the surrounding area. On average, more than 270 breast cancer surgeries are performed each year. Recruitment for this study begins in October 2022 and is expected to continue until 2024. A sufficient source of patients is available to ensure the completion of the recruitment of 160 eligible participants. The trial is currently in the recruitment phase and patients will be screened according to strict recruitment criteria. Prospective participants will be sourced from a surgical waiting list. Screening will be done by reviewing their health records to determine eligibility. Patients will be recruited after admission to the hospital and 1 day prior to surgery.

## Assignment of interventions: allocation

### Sequence generation {16a}

Random sequences are generated on a 1:1 basis using a computerised random number generator and researchers placed the random sequences in sealed, opaque and sequentially numbered envelopes. When participants are eligible for the study and allowed into the surgical preparation room, the researcher will open the envelope to obtain the random sequence that determined the grouping. Each participant will correspond to a unique random sequence number in an envelope in the order in which they participated in this study. The numbered information of all participants will be recorded in the randomised list.

### Concealment mechanism {16b}

The participant’s unique randomised serial number and group allocation information will be printed on a separate sheet of paper and stored confidentially. The person performing the randomisation assignment and the nerve block operator will not be involved in the subsequent study process.

### Implementation {16c}

The randomisation described above will determine whether to perform a nerve block or a sham nerve block. Once participants enter the surgical preparation room to determine the grouping, the researcher will perform the nerve block based on the grouping. The person responsible for the randomisation allocation will carry the envelope of the randomised sequence with the nurse who is not involved in the study to reveal the results of the grouping of participants.

## Assignment of interventions: blinding

### Who will be blinded {17a}

Due to the nature of the intervention in this study, the person responsible for the randomisation process and the nerve block operator will be the unblinded study personnel. Therefore, participants, anaesthetists, surgeons, post-operative follow-up staff and nerve block effect assessors will be unaware of the random allocation sequence.

### Procedure for unblinding if needed {17b}

To enable investigators to know the study group of participants in the event of an emergency, a 24-h unblinding telephone number is available. In the event of a medical emergency that may be relevant to this trial, the need for unblinding will be discussed by the principal investigator and, if indeed necessary, a rapid emergency unblinding can be carried out via the unblinding telephone number. The study team leader and ethics committee must be informed as soon as possible after the unblinding has taken place. The time, reason and outcome of the unblinding must be documented in the source document.

### Plans to promote participant retention and complete follow-up {18b}

Participants will be fully informed and educated by the investigators in a variety of ways to understand the purpose of the trial and the benefits of accelerated recovery. Rationalise the process to minimise the time patients have to wait in the operating room. Ensure that participants have a relatively quiet environment for ESPB and follow-up visits, which will be limited to 3–5 min to protect patient privacy and rest. During the course of the trial, subjects are made aware of the possible adverse reactions to avoid shedding due to minor or normal adverse reactions. Strengthen the training of investigators who have a thorough understanding of the clinical trial, are familiar with the trial protocol, can answer patients' questions accurately and reasonably and establish a good doctor-patient relationship, thus making patients more comfortable with the trial.

Participants have the right to withdraw from the study at any time for any reason. Reasons for withdrawal will be asked, measured and recorded in the source documents, and the Ethics Committee will be informed.

### Data management {19}

This study will manage data in accordance with the Data Security Law of People’s Republic of China and the European Union’s General Data Protection Regulation [13]. Follow the principles of “clear purpose” and “minimum collection”. All research data will be filled in manually in paper CRFs. CRFs recording the data will be kept in a locked safe and then transcribed into Microsoft Excel by researchers not involved in the implementation of the intervention, who will use an offline computer to aggregate and analyse the data. To improve the quality and accuracy of the data, a data monitoring team consisting of an anaesthetist, a statistician and a nurse was set up. All data are checked for errors and those suspected of being incorrect are re-verified. Access to safe and computer is restricted to researchers assigned to the work of data entry, processing and analysis.

### Confidentiality {27}

During the trial, all paper patient information will be stored in strict confidentiality in a secure safe. All electronic information relating to the study will be stored offline on a computer. In order to protect the privacy of participants, any access to the safe and the computer will be strictly reviewed and authorised before viewing. Participants’ research information will not be used for purposes other than research without written permission. Anonymous trial data may only be shared with other researchers with the author’s consent and only for research purposes.

### Plans for collection, laboratory evaluation and storage of biological specimens for genetic or molecular analysis in this trial/future use {33}

Blood specimens collected for this study will be managed in accordance with the ethical and legal requirements of local and the International Organization for Standardization [14]. In order to determine the potential beneficial effect of continuous ESPB in reducing the inflammatory response after MRM surgery, participants will be studied for inflammation-related cytokines. Blood levels of inflammatory cytokines will be measured 1 day before surgery, 2, 6, 12, 24 and 48 h after surgery. Cytokines to be measured include pro-inflammatory cytokines (TNF-α, IL-6) and anti-inflammatory cytokines (IL-10). From a safety perspective, plasma concentrations of ropivacaine will be analysed on days 1, 2 and 3 after surgery. All blood samples will be sent to our central laboratory promptly after acquisition and centrifuged within 1 h, and plasma will be separated and stored at − 80 °C for analysis later in the trial. All plasma samples will be discarded upon completion of the study.

## Statistical methods

### Statistical methods for primary and secondary outcomes {20a}

Statistical analysis will be performed using SPSS statistical software version 27.0 (IBM). All statistical tests will be two-tailed and the significance level will be set at 0.05. Primary and secondary outcomes will be analysed using the following statistical method: the Kolmogorov–Smirnov test will be used to determine whether continuous data follow a normal distribution, and the Levene’s test was used to assess the homogeneity of variance. Normally distributed continuous data are expressed as mean ± standard deviation and compared using the independent samples* t*-test. Non-normally distributed continuous data will be expressed as median and interquartile range and compared by the Mann–Whitney *U* test. Count data is expressed as the number of cases (rate) by the chi-square test or Fisher’s exact test.

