### Methods for additional analyses (e.g. subgroup analyses) {20b}

Not applicable, no additional analysis is planned for this study.

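### The serial cytokines are assigned to unadjusted two-sample tests that leave the collected baseline unused and give no single estimate of the inflammatory effect

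*Protocol article*

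**What the plan says.** In the protocol article, the section on statistical methods for primary and secondary outcomes {20a} opens its analysis rule with "Primary and secondary outcomes will be analysed using the following statistical method". A Kolmogorov–Smirnov test decides which of two branches applies to continuous data. The first branch is a t-test: "Normally distributed continuous data are expressed as mean ± standard deviation and compared using the independent samples". The second, for data that fail the normality check, reports medians and uses the Mann–Whitney test.

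Counts go to a chi-square or Fisher test. On error rate it says: "All statistical tests will be two-tailed and the significance level will be set at 0.05". It names no covariate, repeated-measures model or summary over time, and it does not label secondary results as descriptive or exploratory.

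The Secondary outcomes section lists four markers (TNF-α, IL-10, IL-6 and CRP), with sampling times given as "in venous blood 1 day before, 2, 6, 12, 24 and 48" (the last five being hours from the operation). The specimen section {33} confirms the preoperative sample: "Blood levels of inflammatory cytokines will be measured 1 day before surgery". Static and dynamic VAS are each taken at five times and QoR-15 at three. PMPS is recorded at 3, 6 and 12 months according to the outcome collection section {18a}.

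**The concern.** The data are longitudinal with a baseline, and the only methods assigned to them are cross-sectional and use no baseline. Three consequences follow.

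1. Every participant gives a preoperative blood sample whose cytokine values enter no stated analysis. If those values predict the postoperative ones, precision is given away.
2. Inflammatory response is in the registered title and in the main aim under Objectives {7}. Five separate tests per marker do not add up to one estimate of the effect on inflammation over 48 h.
3. If the normality pre-test is applied time by time, one marker could be summarised by a mean at one hour and a median at the next, so its course could not be read on one scale.

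The same structure affects static and dynamic pain and QoR-15. With no named contrast and no descriptive label, the plan does not say how an isolated significant time point is to be interpreted.

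**Working it through.** **The plan's own figure.** The document states no number of secondary comparisons and no gain from baseline adjustment. Its only sizing figure is 71 per group, for one comparison (dynamic VAS at 48 h, 4.2 ± 1.4 versus 3.6 ± 1.1, two-sided 0.05, 80% power). That figure reproduces: the pooled SD is √[(1.4² + 1.1²)/2] = 1.259, and a noncentral-t calculation gives 79.9% power at 70 and 80.5% at 71. Allowing 11% dropout, 71/0.89 rounds up to 80. It is not in dispute here and does not bear on the cytokines.

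**Gain from using the baseline.** Let ρ be the within-arm correlation between log baseline and the log postoperative value analysed. The documents give no ρ, so these values are assumptions. Adjustment leaves a fraction 1 − ρ² of the unadjusted variance. The equivalent increase in sample is 1/(1 − ρ²) − 1.

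| Assumed ρ | Variance remaining | Variance cut | Equivalent extra patients |
|---|---|---|---|
| 0.1 | 0.99 | 1% | about 1% |
| 0.2 | 0.96 | 4% | about 4% |
| 0.3 | 0.91 | 9% | about 10% |
| 0.5 | 0.75 | 25% | about 33% |
| 0.7 | 0.51 | 49% | about 96% |

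**Number of comparisons if each time is tested.**

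- VAS: 2 conditions × 5 times = 10
- Inflammatory markers: 4 × 5 postoperative times = 20
- QoR-15: 3
- PMPS: 3
- Total: 10 + 20 + 3 + 3 = 36

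Without CRP the markers give 3 × 5 = 15, and the total is 31.

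**False positives if there is no effect on any of them.**

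- Expected number: 36 × 0.05 = 1.8 (31 × 0.05 = 1.55). This holds whatever the correlation.
- Chance of at least one if independent: 1 − 0.95³⁶ = 84%.
- Chance of at least one if tests are correlated within each series (static VAS, dynamic VAS, each marker, QoR-15, PMPS) and the series are independent of one another: 77%, 70% and 56% at assumed correlations of 0.5, 0.7 and 0.9, by simulation with 200,000 replicates.
- If the series were also correlated with one another, the chance would be lower: with one common correlation across all 36 tests, simulation gives 72%, 55% and 36% at 0.3, 0.5 and 0.7.

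**The case against.** **It is not invalid.** A two-sample comparison at a single time is valid in a randomised trial, and leaving out the baseline does not bias it. This stands. A reader might infer that the planned cytokine results would be biased; nothing in the document supports that. The loss is in precision and interpretability.

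**It belongs in a statistical analysis plan.** Covariates and longitudinal models are often left to one, and this article condenses a fuller protocol. That would answer a section that was silent. This section instead assigns a named set of methods to all primary and secondary outcomes, so the point concerns a stated choice.

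**The text never says that each time is tested separately.** Correct; that is an inference. It rests on the outcomes being listed by time and two-sample tests being the only tools named for them.

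**The article rules out anything further.** A reader might infer this from "Not applicable, no additional analysis is planned for this study". That sentence sits under a heading about subgroup-type analyses, and the missing-data section {20c} itself plans a sensitivity analysis. It does not settle how the serial outcomes are modelled, and the point does not rely on it.

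**Secondary outcomes need no family-wise control.** This is a fair position. One primary outcome is named and all of these outcomes are labelled secondary. The error-rate figures show why per-time results should be labelled descriptive; they do not show that a correction is obligatory.

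**The marker lists conflict.** A reader might infer a contradiction because CRP is an outcome but is absent from the assay lists in {26b} and {33}. The first lists markers run on ELISA kits, and the second says only what the cytokines include. This is a minor wording inconsistency that affects the count (36 or 31) and not the method.

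**The gain may be small.** This also stands. A sample taken the day before surgery may predict the postoperative response weakly, and the documents do not settle how strongly.

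**Conclusion.** The point holds as one of efficiency and interpretability in the secondary analyses. The stated method leaves the preoperative cytokine values unused and gives no single estimate of the inflammatory effect. The precision at stake ranges from negligible (1–4% of variance at a correlation of 0.1–0.2) to large (49% at 0.7), and all of these correlations are assumed. The lack of a summary estimate does not depend on the correlation; it depends only on reading the methods section as separate comparisons by time.

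On that reading there are 36 comparisons (31 if CRP is not assayed) and about 1.8 expected false positives if there is no effect. The chance of at least one is roughly 56–84%, from strong within-series correlation up to independence, and lower if the series are also correlated with one another. A reader might take 84% as the trial's error rate, but it is the independence case and serial measurements are not independent. The primary outcome, cumulative PCA consumption, is not affected.

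**What to change.** In {20a}:

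- Analyse each log-transformed marker with one mixed model containing arm, time (as a category), arm-by-time and log baseline. Report the arm ratio averaged over 2–48 h with a 95% CI.
- Use the same model without a baseline term, on the original scale, for static VAS, dynamic VAS and QoR-15. Report the arm difference averaged over the scheduled times with a 95% CI.
- State that comparisons at individual times are descriptive.

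Naming the model in advance also removes the normality pre-test's role in choosing the analysis for these outcomes.

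The cost is a few sentences of wording and slightly more analysis work. No new samples, visits or participants are needed, and the named software, SPSS 27.0, fits such models. According to {18a}, analysis begins after the last participant has completed the trial, so the change can be made before unblinding.
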